## Statistical analysis

### Primary aims

Since our primary aims are descriptive, they will be presented as frequencies, percentages, means and SDs as appropriate. Missing data will be calculated as the percentage amount of data available from the total amount of expected data. Engagement will be assessed through data availability in passive data streams and data quality will be measured as the number of active tasks that are incomplete. Associations between engagement and clinical characteristics will be explored. Recordings of the semistructured interviews will be transcribed verbatim, checked for accuracy by a second researcher and analysed using a deductive approach to thematic analysis, with the iterative categorisation technique.^43^ Where participant responses can be quantified, they will be presented as aggregated counts or percentages, otherwise, summaries of participant responses will be presented narratively. Sporadic reports of issues with the technology or study methodologies will be summarised.

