**Methods and analysis:**

This is an observational, prospective cohort study of 65 people attending psychological therapy for depression in multiple London-based sites. It will collect continuous passive data from smartphone sensors and a Fitbit fitness tracker, and deliver questionnaires, speech tasks and cognitive assessments through smartphone-based apps. Objective data on sleep, physical activity, location, Bluetooth contact, smartphone use and heart rate will be gathered for 7 months, and compared with clinical and contextual data. A mixed methods design, including a qualitative interview of patient experiences, will be used to evaluate key feasibility indicators, digital phenotypes of depression and therapy prognosis. Patient and public involvement was sought for participant-facing documents and the study design of the current research proposal.

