## Methods and analysis

### Design

This is an observational, prospective cohort study of people attending psychological therapy for depression. It will use RMTs to gather active and passive data for up to 7 months and will adopt a mixed methods design to evaluate the feasibility and acceptability of such data collection methods.

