**Passive measures**					
Fitbit Charge	To be worn throughout the study.				
pRMT app: GPS, acceleration, light, phone interaction, Bluetooth devices, number of contacts, battery level, weather	Will run in the background gathering data from enrolment.				
**Qualitative interview**†					x

*Weekly time spent completing questionnaires should not exceed 10 min.

†Completed once during treatment.

‡Only for the duration of treatment.

§Daily for 90 days.

ADDS, Atypical Depression Diagnostic Scale; aRMT, active RMT; AUDIT, Alcohol Use Disorder Identification Test; BIPQ, Brief Illness Perceptions Questionnaire; CTQ, Childhood Trauma Questionnaire; GAD-7, Generalized Anxiety Disorder; GSP, Global Positioning System; MINI, Mini International Neuropsychiatric Interview; PHQ-9, Patient Health Questionnaire; pRMT, passive RMT; QIDS-SR, Quick Inventory of Depressive Symptomatology-Self-Report; REDCap, Research Electronic Data Capture; RRS, Rumination Response Scale; SAPAS, Standardised Assessment of Personality: Abbreviated Scale; SRRS, Social Readjustment Rating Scale; WAI-SR, Working Alliance Inventory-Short Revised; WSAS, Work and Social Adjustment Scale.

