#### End of study

Twelve weeks after participants have finished treatment, the research team will contact them to finalise their time in the study and complete endpoint assessments. In case of an unexpected change regarding their treatment, such as treatment being reduced or extended, the 3-month follow-up will commence on the day of their last core treatment session with IAPT services.

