### Outcome measures

#### Primary outcomes

The primary outcome is to establish the feasibility of using wearable devices and smartphone sensors to monitor the behaviour of people with depression while receiving psychological treatment. Key feasibility outcomes will be related to clinical and methodological considerations, and will evaluate recruitment and participant flow, subjective reports of acceptability of methods, data availability and data quality.

The following feasibility outcomes will be reported:

Estimates of recruitment and attrition rates (figure 2).Presence and absence of passive data: ‘wear time’ for wearable devices and ‘on time’ for smartphone sensors, and the extent to which the available data allow for correlational and predictive analyses with significant statistical power.Active data availability and data quality: percentage number of tasks completed.Qualitative data: participant experience and attitudes towards data collection instruments and procedures.

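### The primary analysis labels the share of data available as missing data, and active tasks are scored as a percentage completed in one section and a raw count incomplete in another

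*Protocol article*

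**What the plan says.** The primary outcome is feasibility, and data availability and data quality are among its components. Under Statistical analysis, Primary aims, the rule for missing data is: "Missing data will be calculated as the percentage amount of data available from the total amount of expected data". For active tasks the same section says "data quality will be measured as the number of active tasks that are incomplete". Under Outcome measures, Primary outcomes, the corresponding entry is "Active data availability and data quality: percentage number of tasks completed".

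The length of observation, which sets the expected amount of data, is described in three ways. The abstract says that data up to and including "heart rate will be gathered for 7 months". The Design section says "It will use RMTs to gather active and passive data for up to 7 months". The End of study section says "Twelve weeks after participants have finished treatment, the research team will contact them to finalise their time in the study", and starts that clock at the last core session if treatment turns out shorter or longer than planned.

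In Table 1 the perceived-sleep task is marked in the weekly column, and the Active measures text lists it among the weekly app tasks. Its footnote reads "Daily for 90 days".

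Under Secondary aims, multiple imputation is planned where data are missing at random and the amount missing is not too large. Otherwise missingness may be used as a predictor.

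**The concern.** Two stated rules give a wrong or poorer result if followed as written.

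First, the quantity named missing data is its complement. It describes a primary feasibility outcome, and the choice between imputing and modelling missingness depends on how much is missing. Under the literal definition, nearly complete data would count as heavily missing and could be sent down the wrong branch.

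Second, the active-task outcome has two definitions that run in opposite directions and on different scales. A percentage carries its own denominator and a count does not. Observation time differs between participants, so a count of incomplete tasks rises with time in study even when adherence is the same. The plan also intends to explore associations between engagement and clinical characteristics, and to model whether clinical data predict missing-data patterns. A count used there would partly measure length of treatment.

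The Study aims section gives the description of engagement and missing data as the purpose of the work, because both bear on future large studies. These are therefore figures that others are meant to use.

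**Working it through.** The plan gives no numerical value for completeness, so there is no figure of its own to reproduce on this point. Its sample-size figure is not affected.

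**1. The inverted label.** As written, missing % = 100 × available / expected. The correct form is missing % = 100 × (expected − available) / expected.

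| Available | Reported as missing, as written | Actually missing |
|---|---|---|
| 50% | 50% | 50% |
| 60% | 60% | 40% |
| 80% | 80% | 20% |
| 90% | 90% | 10% |

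The two agree only at 50%.

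**2. Observation time.** Inputs from the plan are a wait of 1 to 5 weeks before treatment (Inclusion criteria) and 12 weeks after it (End of study). Treatment length is not stated; I assume 6 to 20 weeks.
- Shortest: 1 + 6 + 12 = 19 weeks.
- Longest: 5 + 20 + 12 = 37 weeks.
- Seven months: 7 × 365.25 / 12 / 7 = 30.4 weeks.
- Treatment length at which the two descriptions coincide: 30.4 − 12 − 1 = 17.4 weeks, down to 30.4 − 12 − 5 = 13.4 weeks.

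**3. Count against percentage.** Take one weekly questionnaire (the QIDS-SR) and two participants who stay to their own endpoint and each complete 80%.
- 19 weeks: 0.20 × 19 = 3.8 incomplete.
- 37 weeks: 0.20 × 37 = 7.4 incomplete, a ratio of 37 / 19 = 1.95.
- If 7 months is a ceiling, about 30 weeks: 0.20 × 30 = 6.0 incomplete, a ratio of 30 / 19 = 1.58.

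The percentage completed is 80% in every case. This comparison needs no assumption about withdrawals.

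**4. Why the denominator should be named.** Assume a planned window of 30 weeks and a participant who completes 80% of tasks and leaves at week 8. Completeness is 80% of tasks due before withdrawal, or 0.80 × 8 / 30 = 21% of the planned window.

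For the cohort, take 65 enrolled and the plan's 20% attrition, so 13 leave at week d and 52 stay, all at 80% while in the study. Completeness against the planned window is (52 × 30 × 0.8 + 13 × d × 0.8) / (65 × 30):
- d = 4: 66.1%
- d = 8: 68.3%
- d = 15: 72.0%

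The until-withdrawal figure is 80% throughout.

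**5. The sleep task.** The footnote gives 90 expected entries; a weekly task over 7 months gives about 30. Twenty completed entries, as an illustration, are 20 / 90 = 22% or 20 / 30 = 67%.

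**The case against.** The strongest reply is that the first fault is a slip in one sentence. The formula is spelled out beside the label, the Primary outcomes section has the direction right, and a result headed as data available would be read correctly. That stands as far as it goes: a reader might infer that the published result will mislead, and the documents do not show that. The sentence is still the stated analysis rule, and the imputation choice depends on the same quantity.

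On the count, the reply is that percentage completed and number incomplete are complements, and that the analysis section allows percentages as appropriate. They convert only with a fixed denominator, and only if incomplete means not completed; it could also mean begun but unfinished. The mismatch therefore remains.

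On the denominator, the reply is largely right. The Design and End of study sections together allow expected tasks to be counted per participant, no treatment length is stated that would make the periods contradict outright, and the sleep footnote reads naturally as overriding the weekly mark. Detailed counting rules may also sit in a fuller document. What remains is a need to reconcile the wording.

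Several stronger readings are tempting but not supported:
- A reader might infer that an early drop-out with 0 of 20 tasks done looks like a completer with 150 of 172 done, since 20 and 22 are incomplete. That assumes expected tasks stop at withdrawal, which the plan does not say. Counted to the planned end, it is 172 against 22. Attrition is also reported as its own outcome.
- A reader might infer that the sleep frequency shifts an overall app-task completion rate. No section describes such a pooled rate.
- A reader might infer that no quality is measured, or that engagement ignores active tasks. The Primary outcomes section lists active and passive data separately and also asks whether the data can support the planned analyses.

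**Conclusion.** The concern holds in a limited form. The definition of missing data is inverted as written, and the active-task outcome is stated in two incompatible ways, one of which is not comparable between participants. The inversion turns 20% missing into 80%. The count differs by a factor of up to about 1.6 to 1.95 at identical adherence. Those factors rest on the assumed treatment length of 6 to 20 weeks, and the lower one on treating 7 months as a ceiling. The withdrawal figures (80% against 66% to 72%) further assume a 30-week window, 80% adherence while in the study and the plan's 20% attrition. They show why the denominator should be named; they are not evidence of an error.

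The follow-up and sleep-task statements need to be made consistent, but they do not make the expected total impossible to count. The results can be misread; that they will be is not established. Sample size and data collection are unaffected.

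**What to change.** - In Statistical analysis, Primary aims, define completeness as completed (or available) divided by expected, and missingness as one minus that, for each participant and each data stream.
- Replace the count of incomplete active tasks with the percentage completed, so that this section and Primary outcomes use the same measure.
- Report completeness against the planned follow-up window with drop-outs included, and give the until-withdrawal version as a second figure.
- Reconcile the three statements of follow-up length, and the weekly and daily descriptions of the sleep task, so that one denominator applies throughout.

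The cost is rewording and a little analysis code, with no new data. The drawback is that the main completeness figure will look less favourable than one counted only to withdrawal.

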### Secondary aims

Digital features that account for sleep, activity, sociability and cognition will be extracted from sensor data and correlated against scores on scales of depression, anxiety and functionality. Feature extraction will replicate the methods used by the RADAR-CNS consortium.^23 44^ Regression or classification analyses will be carried out for clinical scores to see whether higher impairment is associated with behavioural features. Regression and classification approaches will also be used to determine whether clinical data predict subject attrition or missing data patterns.

We will carry out univariate and multivariate associations on digital features and clinical state, as well as within and between individual comparisons. In order to unearth digital profiles in the sample, individuals will be clustered together based on their response patterns using latent class analysis. This person-centred approach will unpick some of the heterogeneity in the sample and assumes there are underlying latent variables that underpin distinct symptom profiles,^45^ and has been used extensively in the construction of the subtypes of depression.^46^ This model will aid in the description of longitudinal behavioural patterns in this sample.

To evaluate the prognostic value of digital features, we will use machine learning methods on the extracted aggregated features and clinical information, provided there are sufficient data points. A multivariate prediction model will be constructed, and different feature selection algorithms will be applied. Model performance will be evaluated through cross-validation, putting stress on sensitivity and specificity of relapse prediction model. We will also use dynamic structural equation modelling to evaluate the lagged associations across study time points.

Where data are missing at random and assuming it is not significantly high, multiple imputation methods will be carried out. If missing data are high, this may be incorporated into the model as a predictor, or otherwise used informatively.

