### Study aims

The primary aim of this project is to evaluate the extent to which data collection with digital tools on clinical samples is feasible. Specifically, the feasibility of using RMTs, such as Android smartphones and a Fitbit wearable device, to collect behavioural and clinical data in people undergoing therapy for depressive disorders, to establish the extent to which they can be potentially useful biomarkers of depression and changes in clinical state. The purpose of this is to describe patterns of user engagement and missing data, which are likely to impact the scientific integrity of future large-scale studies.

Secondary aims are to identify candidate signals for digital biomarkers by detecting correlations between objective features and clinical characteristics, and to explore whether these signals have prognostic value in the context of psychological treatments.

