#### Secondary outcomes

Secondary outcomes will evaluate the relationship between digital data and clinical outcome measures, both at individual time points and as prognostic factors for recovery after treatment. Scores on clinical scales will be used in addition to individual symptom domains.

Digital outcomes will be derived from smartphone and Fitbit sensors, and digital features from passive measures described in the ‘Passive Measures’ section, such as GPS signal patterns, sleep, phone use and Bluetooth interactions. They will be extracted to form averages that encapsulate daily, weekly and within-treatment means and SDs or frequency counts.

Clinical state will be measured using:

Patient Health Questionnaire (PHQ-9)^30^: the nine-item questionnaire that is widely used for measuring depression in IAPT services.Generalized Anxiety Disorder^31^ questionnaire: will be measured as it gathers important anxiety symptoms which are so often comorbid with depression.Quick Inventory of Depressive Symptomatology-Self-Report (QIDS-SR)^32^: this is a 16-item inventory of depression for patients who identify as depressed or who may be suffering from depression.Work and Social Adjustment Scale^33^: a measure of quality of life/disability, which is a five-item assessment of perceived social and work-related functional impairment used widely across a range of mental and physical disorders.Cognition via the THINC-it app.

Participants will be considered to be in remission if they have experienced a reduction of at least 50% in depressive symptomatology from the start of treatment, or no longer meet criteria for depression according to the PHQ-9 (scoring below the cut-off of 5). Subdimensions of depression—for example, interest in activities, motivation, appetite—will be gathered from the QIDS-SR.

The sociodemographic, clinical and contextual variables measured, such as illness severity, cognitive function and social support, will be taken as covariates.

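### The prognostic value of digital features is judged by the performance of a model that also contains clinical data, with no clinical-only benchmark named

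*Protocol article*

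**What the plan says.** The second of the secondary aims (Study aims) concerns the digital signals themselves: "to explore whether these signals have prognostic value in the context of psychological treatments".

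For that purpose, Statistical analysis, Secondary aims gives inputs, a model and a yardstick:

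- Inputs: "we will use machine learning methods on the extracted aggregated features and clinical information, provided there are sufficient data points".
- Model: "A multivariate prediction model will be constructed, and different feature selection algorithms will be applied".
- Yardstick: "Model performance will be evaluated through cross-validation, putting stress on sensitivity and specificity of relapse prediction model".

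Secondary outcomes adds three relevant facts. Sociodemographic, clinical and contextual variables, "such as illness severity, cognitive function and social support, will be taken as covariates". Remission is defined as "a reduction of at least 50% in depressive symptomatology from the start of treatment, or no longer meet criteria for depression" on the PHQ-9 (a score below 5). Digital features are summarised as "daily, weekly and within-treatment means and SDs or frequency counts".

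Two other parts of the plan come near the question. Secondary aims also states: "We will also use dynamic structural equation modelling to evaluate the lagged associations across study time points". Reporting standards promises a full account of model selection strategy, performance metrics and parameter estimates with confidence intervals.

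**The concern.** The question is about digital signals, but the performance measure belongs to a model that holds digital and clinical inputs together. Good sensitivity and specificity could come from the digital features, from the clinical information or from both, and the pooled figure does not say which.

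The risk is a practical one. Remission depends on the starting score: one route is a halving from the start of treatment, the other is falling below a fixed cut-off. Baseline severity is therefore a natural predictor, and it is among the clinical data collected. A pooled model could predict moderately well on severity alone.

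The study is meant to find candidate digital biomarkers and to inform larger studies. A pooled result read as digital value could carry a misattributed signal into that later work.

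**Working it through.** **1. The plan's own figures.** The article gives no calculation for the prognostic model. Its only sample-size figure is for a correlation (Sample size: r = 0.39, significance level 0.05, type 2 error 0.20, 50 participants; 20% attrition, 65 recruited).

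- Fisher z, two-sided: n = ((1.960 + 0.842) / atanh(0.39))² + 3 = (2.802 / 0.412)² + 3 ≈ 49.3, so 50. This reproduces the stated figure.
- Attrition: 50 / (1 − 0.20) = 62.5, so 63. The stated 65 is slightly more generous.
- Expected to remain: 65 × 0.80 = 52.

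These figures are sound. They matter here only because they set the sample for the prognostic model at about 52.

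**2. Can pooled performance look good when digital features add nothing?** This was checked by simulation. The following inputs are assumptions, because the documents do not give them:

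- one baseline severity score, with log-odds of the outcome of 1.0 or 1.5 per SD;
- an event rate of about 50%;
- five digital features with no effect on the outcome given severity, correlated 0 or 0.39 with severity;
- a ridge logistic model with five-fold cross-validation and one row per participant;
- 300 replicates at n = 52 and 60 at n = 1000.

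AUC stands in for sensitivity and specificity, since it summarises both across all thresholds. Mean cross-validated AUC:

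| n | Log-odds per SD | Correlation with severity | Pooled | Clinical-only | Digital-only | SD of (pooled − clinical) |
|---|---|---|---|---|---|---|
| 52 | 1.0 | 0 | 0.638 | 0.689 | 0.458 | 0.072 |
| 52 | 1.0 | 0.39 | 0.647 | 0.686 | 0.577 | 0.077 |
| 52 | 1.5 | 0 | 0.733 | 0.777 | 0.466 | 0.055 |
| 52 | 1.5 | 0.39 | 0.739 | 0.775 | 0.624 | 0.049 |
| 1000 | 1.0 | 0 | 0.735 | 0.738 | 0.489 | 0.003 |
| 1000 | 1.0 | 0.39 | 0.733 | 0.736 | 0.653 | 0.004 |
| 1000 | 1.5 | 0 | 0.812 | 0.814 | 0.493 | 0.002 |
| 1000 | 1.5 | 0.39 | 0.809 | 0.811 | 0.704 | 0.003 |

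**3. Reading the table.** At n = 52 the pooled model reaches 0.64 to 0.74 although the digital features add nothing. Pooled minus clinical-only is −0.051, −0.039, −0.044 and −0.036 in the four rows, so the extra inputs slightly worsen prediction. The pooled figure alone shows none of this; the clinical-only column does. The problem is not one of small samples: at n = 1000 the pooled model reaches 0.73 to 0.81, again with no digital contribution.

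**4. Does another planned analysis supply the comparison?**

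- Covariate adjustment and parameter estimates describe adjusted associations of single features.
- Dynamic structural equation modelling describes lagged associations over time.
- The univariate and multivariate associations relate features to clinical state.

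None of these sets prediction with the digital features against prediction without them.

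**The case against.** The article is condensed, and a fuller plan may name a benchmark. Saying that a prediction model will be built does not say that only one will be fitted, and the promise to describe model selection suggests that candidates will be compared. Adjusted estimates and the lagged models do give some evidence on digital features. The aim is secondary and exploratory, and the model depends on there being enough data. The simulation rests on assumed inputs, and the benchmark comparison would be imprecise.

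Much of this stands and limits the point. It does not remove it, because the article states purpose, inputs and yardstick for this analysis, and the yardstick does not measure the purpose. That is a mismatch in what is written, not a detail left to another document. Reading prognostic value as unadjusted value does not help either: the pooled figure does not isolate that quantity.

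A reader might infer more than the documents support:

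- **Leakage between folds.** The condition on sufficient data points might suggest that weekly rows from one person will be split across folds. The article names aggregated features and does not say that rows are the unit.
- **Selection outside the folds, or reporting the best of several pipelines.** The article says that feature selection algorithms will be applied and performance cross-validated. It does not say that selection comes first or that only the best result is reported.
- **Features that record response rather than forecast it.** Within-treatment summaries are listed for the secondary outcomes in general and are not assigned to the prognostic model. End of study places the endpoint 12 weeks after treatment, and for an outcome measured then, within-treatment features come first. The point is conditional on which outcome and features are used.

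**Conclusion.** The point holds in a limited form. Followed as written, the evaluation yields a performance figure that cannot be attributed to the digital features, and no planned analysis compares prediction with and without them. Under the stated assumptions a pooled AUC of about 0.64 to 0.74 at n = 52 is compatible with digital features that add nothing, against 0.69 to 0.78 for severity alone. These values illustrate the mechanism; the true event rate, strength of severity and number of features are not in the documents.

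Two stronger conclusions are not supported. One is that the study cannot address its prognostic aim at all: the adjusted estimates and lagged models give indirect evidence. The other is that a false biomarker claim is the likely result: it is possible, but the aim is exploratory and the article already says that its design limits conclusions about digital changes to treatment response. The change is worth making because it is cheap and matches the measure to the aim.

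**What to change.** - Fit two models on the same participant-level folds: a clinical-only model (pre-treatment severity and a few baseline items) and a clinical-plus-digital model.
- Keep feature selection inside the folds.
- Report the difference in performance, with a participant-level bootstrap confidence interval, as the measure of digital prognostic value. The planned sensitivity and specificity can be reported for both models.
- If within-treatment summaries enter the prognostic model, use only features recorded before the period over which the outcome is assessed.
- Label the result exploratory.

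**Cost.** A little more analysis, with no new data, participants or procedures. The difference will be imprecise: with a simulated SD of 0.049 to 0.077 at n = 52, 1.96 × SD is about 0.10 to 0.15 on the AUC scale. The comparison will seldom settle added value in this study, but its interval will show how little or how much the data can say.

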## Introduction

Depression is a leading cause of disability worldwide,^1^ yet response to treatment is poor, with only 50%–60% of people recovering after 3 months of treatment.^2 3^ Mental health science relies almost exclusively on subjective self-report to diagnose mental illness and measure outcomes. Reliance is therefore placed on patients being able to accurately recall and communicate complex mood states during clinical interviews, which many patients find difficult.^4 5^ Depending on subjective methods introduces a vulnerability to recall biases^6^ which may worsen with increased severity.^7^

The use of digital tools within mental health has the potential to enhance traditional self-report measures by improving aspects of symptom tracking, illness management and treatment support. Remote measurement technologies (RMTs) such as smartphones and wearable devices can unobtrusively capture a more accurate picture of a patient’s clinical state in a continuous way, with far less burden to the user. Through embedded sensors, they can detect changes in behaviours associated with depressive symptomatology such as sleep,^8^ sociability,^9^ physical activity^10^ and speech.^11^ Detecting such changes in a person’s behaviour can provide invaluable information for tailoring and improving treatment.

Given the relative recency of the field, and with an eye towards clinical implementation, studies on RMTs and depression have largely comprised proof-of-concept, feasibility and acceptability studies. While studies show RMTs to be generally feasible and acceptable,^12^ the data predominantly come from small, non-clinical or student samples with a median follow-up time of 2 weeks.^13^

To our knowledge, no such feasibility studies have been published on the use of RMTs to track mood and behaviour in clinical populations undergoing psychotherapy for depression. This population could derive greater benefits from the application of such digital methods by alleviating distress in more potentially severe cases and reducing pressure on healthcare services. In addition to the barriers of adopting RMTs for mood monitoring found across populations, such as concerns around privacy, confidentiality, affordability and accessibility, there are likely to be additional considerations related to the help-seeking populations that remain unexplored and may help or hinder implementation practices in the future.

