#### Inclusion criteria

Adults with a current depressive episode as measured by the Mini International Neuropsychiatric Interview (MINI^19^).Being on the waiting list to receive treatment for depression at IAPT services, with an expected wait of at least 7 days (to a maximum of 5 weeks) between scheduled enrolment and first treatment session. Due to the prevalent comorbidity with anxiety disorders, people with a main diagnosis of anxiety were also included, provided they met inclusion criterion A.Existing ownership of Android smartphone with sufficient memory space for the relevant apps.Able and willing to use a wrist-worn device for duration of the study.Able to give informed consent for participation.Sufficient English language skills to understand consent process and questionnaires.

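### The prognostic model is to be judged on sensitivity and specificity for relapse, but the outcomes section sets recovery after treatment as the prognostic outcome and defines only remission

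*Protocol article*

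**What the plan says.** The Study aims section gives the prognostic aim in general terms: "to explore whether these signals have prognostic value in the context of psychological treatments". Secondary outcomes makes it specific. Digital data will be related to clinical measures "both at individual time points and as prognostic factors for recovery after treatment". The Abstract likewise speaks of recovery after treatment.

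Secondary outcomes then defines one binary clinical outcome: "Participants will be considered to be in remission if they have experienced a reduction of at least 50% in depressive symptomatology", counted from the start of treatment, or alternatively a PHQ-9 score under 5.

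In the Statistical analysis, under Secondary aims, the paragraph on the prognostic value of digital features plans a multivariate prediction model by machine learning, on condition that the data suffice. It ends: "Model performance will be evaluated through cross-validation, putting stress on sensitivity and specificity of relapse prediction model".

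The only other use of the word relapse in the article is inside the expanded name of the RADAR-CNS programme, under Technology set-up.

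**The concern.** Recovery and relapse are different events in different groups of people. Recovery can be assessed in everyone who starts treatment. Relapse can occur only after remission, because the first inclusion criterion is "Adults with a current depressive episode as measured by the Mini International Neuropsychiatric Interview".

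If the analysis section is followed as written, the performance measures singled out for emphasis describe an event that is not among the outcomes, in a subset selected for having responded. Participants who never remit are neither relapse cases nor relapse-free, so they fall out of the calculation. They are the people a model of treatment prognosis most needs to identify.

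A further risk is that, with two candidate events in the text, the target could be chosen after the data are seen. That would sit badly with the article's own commitment under Reporting standards to transparent model reporting.

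**Working it through.** **1. The plan's own figure.** The Sample size section gives 50 analysable participants for a correlation of 0.39, alpha 0.05 and type 2 error 0.20. By the Fisher z method, two-sided:

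n = ((1.960 + 0.842) / atanh(0.39))² + 3 = (2.802 / 0.412)² + 3 ≈ 49.3, rounded up to 50.

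This reproduces. Allowing for 20% attrition, 50 / 0.8 = 62.5, so 63; the plan recruits 65, and 65 × 0.8 = 52. The analysable number is therefore 50–52. It was set for a correlation, not for a classifier.

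**2. Who could relapse.** The Introduction cites "only 50%–60% of people recovering after 3 months of treatment". Used here as a working rate:

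- lower end: 50 × 0.50 = 25
- upper end: 52 × 0.60 = 31.2, about 31

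So about 25–31 participants would be at risk of relapse. Those left out number 50 − 30 = 20 to 52 − 26 = 26.

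**3. How many would relapse.** The article gives no relapse rate. Taking 10–30% as an assumption:

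- 25 × 0.10 = 2.5
- 31.2 × 0.30 = 9.4

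That is about 3–9 events. Even an assumed 50% gives only 12.5 (of 25) to 15.6 (of 31.2).

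**4. What that does to sensitivity.** Exact (Clopper-Pearson) 95% intervals, for an observed sensitivity as near to 80% as the counts allow:

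| Event predicted | Events | Observed | 95% CI |
|---|---|---|---|
| Relapse | 3 | 2/3 | 0.09–0.99 |
| Relapse | 5 | 4/5 | 0.28–0.99 |
| Relapse | 9 | 7/9 | 0.40–0.97 |
| Recovery | 25 | 20/25 | 0.59–0.93 |
| Recovery | 30 | 24/30 | 0.61–0.92 |

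**5. Whether relapse can be read off the remission definition.** Not without ambiguity. A PHQ-9 falling from 22 to 11 is a 50% reduction and counts as remission, although 11 is well above the cut-off of 5. The definition does not indicate what later score would then count as relapse.

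**The case against.** The strongest reply is that this is one word in an exploratory, conditional analysis. The primary aim is descriptive feasibility and is unaffected. The machine learning runs only if the data suffice, so a handful of events need not lead to a fitted model. The same paragraph speaks of prognostic value generally, and the section also plans regression or classification on clinical scores and lagged modelling. All of this stands and limits the severity. It does not say which event is meant: the condition sets no threshold, and the only performance criterion named for the prognostic model is tied to relapse.

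A reader might infer that the study cannot observe relapse. The article does not support that. The schedule of events has PHQ-9 fortnightly and at endpoint, and QIDS-SR weekly, and follow-up continues after treatment: "Twelve weeks after participants have finished treatment, the research team will contact them to finalise their time in the study". Worsening would be recorded. Nor is relapse confined to those 12 weeks, since remission is measured from the start of treatment and could be reached, and lost, before treatment ends.

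It is also fair that a condensed article may leave an operational definition of relapse to a fuller document, so its absence alone would not be a finding. A definition given elsewhere would still leave the outcomes and analysis sections naming different events.

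Finally, the 50%–60% is a background figure for 3 months of treatment, not this study's expected remission rate under its either/or definition, and recovery is itself estimated imprecisely at this sample size.

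**Conclusion.** The inconsistency is real and needs no assumed rate: the outcomes section names recovery and defines remission, while the analysis section judges the model on relapse. The consequence is a change of at-risk group, from all 50–52 analysable participants to about 25–31, if the cited recovery rate carries over. The count of about 3–9 relapses also rests on an assumed 10–30% rate and only illustrates the scale.

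A reader might go further and conclude that the prognostic aim would go unanswered. That is too strong, because other analyses of clinical scores are planned and the paragraph's general wording is not limited to relapse. The severity is moderate: it affects a secondary, exploratory analysis and leaves the feasibility results untouched.

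**What to change.** In the Statistical analysis, Secondary aims, replace the reference to a relapse prediction model with prediction of the remission outcome defined under Secondary outcomes. State one fixed time for it, either end of treatment or the 12-week endpoint, and report cross-validated sensitivity and specificity with confidence intervals for that outcome.

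If relapse is also intended, list it under Secondary outcomes as a separate exploratory outcome, with its criterion, time window and at-risk set.

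The cost is a change of wording. PHQ-9 is already collected fortnightly and at endpoint, so no extra data are needed. The metrics the authors chose can stay, and a continuous target is not required.
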